## Abstract

**Background:**

A significant limitation of femoral artery access for cardiac interventions is the increased risk of vascular complications and bleeding compared to radial access. Ultrasound (US)-guided femoral access may reduce major vascular complications and bleeding. We aim to determine whether routinely using US guidance for femoral arterial access for coronary angiography or intervention will reduce **B**leeding **A**cademic **R**esearch **C**onsortium (BARC) 2, 3, or 5 bleeding or major vascular complications.

**Methods:**

The **U**ltrasou**n**d Gu**i**dance for **V**ascular Acc**e**ss fo**r** Cardiac Procedure**s**: **A** Randomized Tria**l** (UNIVERSAL) is a multicentre, prospective, open-label, randomized trial with blinded outcomes assessment. Patients undergoing coronary angiography with or without intervention via a femoral approach with fluoroscopic guidance will be randomized 1:1 to US-guided femoral access, compared to no US. The primary outcome is the composite of major bleeding based on the BARC 2, 3, or 5 criteria or major vascular complications within 30 days. The trial is designed to have 80% power and a 2-sided alpha level of 5% to detect a 50% relative risk reduction for the primary outcome based on a control event rate of 14%.

**Results:**

We completed enrollment on April 29, 2022, with 621 randomized patients. The patients had a mean age of 71 years (25.4% female), with a high rate of comorbidities, as follows: 45% had a prior percutaneous coronary intervention; 57% had previous coronary artery bypass surgery; and 18% had peripheral vascular disease.

**Conclusions:**

The UNIVERSAL trial will be one of the largest randomized trials of US-guided femoral access and has the potential to change guidelines and increase US uptake for coronary procedures worldwide.

Although radial access reduces major bleeding events and vascular complications, compared to femoral access, in patients requiring coronary interventions, femoral access is still needed for large-bore procedures or when the radial arteries are too small or occluded.^1^^,^^2^ As a result, strategies to improve the safety of femoral access are needed.

Cannulation above the inguinal ligament is associated with an increase in retroperitoneal hemorrhage, whereas cannulation below the common femoral artery (CFA) bifurcation is associated with an increased risk of arteriovenous fistula formation and pseudoaneurysm.^3^, ^4^, ^5^ The use of ultrasound (US)-guided access showed promise in earlier trials, including the **F**emoral **A**rterial Access with **U**ltra**s**ound **T**rial (FAUST). However, the more recent **S**tandard vs **U**ltrasound-Guided **R**adial and **F**emoral Access in Coronary Angiography and Intervention (SURF) trial showed no reduction in vascular complications or bleeding with US guidance.^6^

Two surveys of interventional cardiologists demonstrated that only 13%-27% of operators routinely used US guidance for femoral access, despite 88% answering that US was available in the catheterization laboratory.^7^^,^^8^ Improving the safety of femoral access is needed, especially as the patients receiving femoral access are a small subset of complex patients for whom radial access is not chosen due to technical reasons. These patients often have the highest bleeding risk.

**U**ltrasou**n**d Gu**i**dance for **V**ascular Acc**e**ss fo**r** Cardiac Procedure**s**: **A** Randomized Tria**l** (UNIVERSAL) was designed as a large simple trial to compare US guidance with no US guidance on a background of fluoroscopic guidance for femoral arterial access for coronary angiography or intervention.

## Primary Objective

The primary objective of the study is to determine whether the use of a US-guided approach compared to no US for femoral arterial access for coronary procedures on a background of fluoroscopic guidance will reduce the rate of the composite outcome of major bleeding, based on the **B**leeding **A**cademic **R**esearch **C**onsortium (BARC) 2, 3, or 5 criteria, or major vascular complications within 30 days.

## Hypothesis

Although fluoroscopy readily identifies the location of the femoral head, US allows the operator to visualize the bifurcation of the common femoral artery into superficial and profunda femoral arteries, theoretically reducing the risk of cannulating above the inguinal ligament and below the bifurcation. Furthermore, US may permit the operator to avoid puncturing areas of heavy calcium and disease, potentially reducing complications during cannulation and with closure devices. Using US may reduce the number of punctures and reduce the risk of puncture of branch vessels or venous structures, thereby potentially reducing bleeding and vascular complications.

## Design

UNIVERSAL is a multicentre, parallel randomized open-label trial with blinded outcome assessment comparing US-guided access to no US guidance in patients undergoing coronary angiography or percutaneous coronary intervention (PCI) on a background of fluoroscopic guidance in both groups. The trial is coordinated by the Population Health Research Institute at Hamilton Health Sciences, McMaster University, Hamilton, Ontario, Canada, and has been approved by local ethics boards. The trial is registered at ClinicalTrials.gov with identifier number NCT03537118. UNIVERSAL is an investigator-initiated trial, and funding was provided by the McMaster University Division of Cardiology Innovation Fund and the Hamilton Health Sciences Foundation.

## Eligibility Criteria

Patients were eligible if they were referred for coronary angiography or PCI with planned femoral access. The only exclusion criteria were being aged ≤ 18 years, having had ST-elevation myocardial infarction as the initial presentation, and the absence of a palpable femoral pulse (Table 1).

**Table 1 tbl1:** Eligibility criteria

Inclusion criteria
1. Patients referred for coronary angiography with planned upfront femoral access
2. Elective and non-ST-segment elevation acute coronary syndrome patients
Exclusion criteria
1. Age ≤ 18 years
2. Absence of palpable femoral pulse
3. ST-elevation myocardial infarction patients

## Randomization

Using a centralized computer randomization service (ROME, Population Health Research Institute, Hamilton, Ontario, Canada), we randomized patients 1:1, stratified by planned closure-device use, to femoral arterial access either with US vs with no US. All patients were to have fluoroscopy of the femoral head prior to puncture, in both groups. We considered patients randomized as soon as the treatment allocation was provided to the operator. Allocation was blinded with a variable block size.

## Operator Requirements

Operator expertise is important for US-guided access.^9^ Operators were required to have completed at least 10 US-guided femoral access procedures and to demonstrate that they had achieved all the steps listed below to demonstrate proficiency.

## Treatment Groups

The treatment groups were as follows: (i) experimental group: US-guided femoral access; (ii) control group: no US.

### US

After locating the femoral head with fluoroscopy, the operator used a sterile covered transducer (5 to 10 MHz linear array) and followed the sequence outlined below.(i)Locate and identify the CFA bifurcation into the superficial and profunda femoral arteries and the femoral head.(ii)Scan for atherosclerosis and identify a site free of anterior calcification and plaque suitable for access.(iii)Perform local anesthesia with xylocaine.(iv)Follow the 18-gauge needle as it enters the artery in the short-axis plane.(v)Confirm the position with wire in the artery before sheath insertion in orthogonal views: long axis over the femoral head and short axis with the wire in the centre of a disease-free cross-section above the bifurcation.(vi)Once the operator is satisfied with the entry site, insert the femoral introducer.

### Control group

After locating the femoral head with fluoroscopy, the operator obtained access through palpation of the femoral artery prior to local anesthetic injection.

## Procedures

For both treatment groups, an observer recorded the number of attempts to access the femoral artery, the time between local anesthesia and insertion of the femoral sheath, and the presence of venipunctures. The location of the introducer was evaluated with a peripheral angiogram in the left anterior oblique (LAO) or right anterior oblique (RAO) projections at the level of the femoral head to assess the relation of the femoral introducer with the femoral head and femoral bifurcation. Micropuncture was not mandated in the trial because the prior randomized **Fe**moral **M**icropuncture **o**r **R**outine **I**ntroducer **S**tudy (FEMORIS, N = 402) did not show a reduction in access-site bleeding.^10^ As a result, the use of micropuncture was left up to the operator and was recorded on case report forms.

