### Other outcomes

The key secondary outcomes include the individual components of the primary outcome. Other outcomes include the number of attempts to achieve arterial puncture, successful CFA cannulation, venipunctures, closure device failure, and the total time to obtain femoral access.

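### The access-time outcome is called a total time, but the recorded interval starts after the ultrasound locating and scanning steps, so it is not a total and its comparison probably leans towards ultrasound

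*Protocol article*

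**What the plan says.** Under Other outcomes, the last item listed is "the total time to obtain femoral access". No definition is attached to it there.

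Under Procedures, an observer recorded, for both groups, "the time between local anesthesia and insertion of the femoral sheath". The article describes no other access interval.

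Under US, the experimental sequence is numbered, and it follows fluoroscopy of the femoral head:
- Step (i): "Locate and identify the CFA bifurcation into the superficial and profunda femoral arteries and the femoral head".
- Step (ii): "Scan for atherosclerosis and identify a site free of anterior calcification and plaque suitable for access".
- Step (iii): "Perform local anesthesia with xylocaine".
- Step (iv): "Follow the 18-gauge needle as it enters the artery in the short-axis plane".
- Step (v): the wire is checked in two perpendicular views before the sheath goes in.
- Step (vi): the sheath is inserted.

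Under Control group, fluoroscopy again comes first. The artery is then palpated, and palpation comes before the anaesthetic.

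**The concern.** A total time to access would ordinarily cover everything the operator does to get the sheath in. Here the clock starts at the anaesthetic, and by then the ultrasound operator has already completed two prescribed imaging steps. Those steps are part of the intervention under test. Every ultrasound patient treated to protocol has them and no control patient does, so randomisation cannot balance their omission.

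What is at stake is how one procedural outcome is read. If the recorded interval were reported as total access time, a result showing ultrasound to be quicker or time-neutral could come partly from where the clock starts. The article itself notes that an earlier factorial trial found procedural differences favouring ultrasound, and it hopes to raise ultrasound use. Readers are therefore likely to look at the efficiency results.

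**Working it through.** The article states no figure for access time, so there is nothing to reproduce. The check places each described step before or after the clock start.

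| Step | Ultrasound arm | Control arm | Timed? |
|---|---|---|---|
| Fluoroscopy of the femoral head | yes | yes | no, both arms |
| Locating the bifurcation (i) | yes | none | no |
| Scanning and choosing a site (ii) | yes | none | no |
| Palpation before anaesthetic | not listed | yes | no |
| Local anaesthetic (iii) | yes | yes | clock starts |
| Needle entry, followed on ultrasound (iv) | yes | needle entry without ultrasound | yes |
| Two-view wire check on ultrasound (v) | yes | none described | yes |
| Sheath insertion (vi) | yes | yes | clock stops |

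Two results follow without any durations. First, the interval is not a total in either arm. Second, the arm-specific work left out is steps (i) and (ii) in one arm and palpation in the other.

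To see the effect on the comparison, write:
- A = mean time for steps (i) and (ii), ultrasound arm;
- P = mean palpation time before the anaesthetic, control arm;
- D_rec = recorded mean difference, ultrasound minus control;
- D_tot = mean difference if timing began after fluoroscopy.

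Then D_tot = D_rec + (A - P). The recorded comparison flatters ultrasound by A - P. That is positive only if A exceeds P.

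Neither A nor P is in the article. Purely as assumptions, take A from 15 to 120 s and P from 5 to 30 s. A - P in seconds is then:

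| A | P = 5 | P = 15 | P = 30 |
|---|---|---|---|
| 15 | 10 | 0 | -15 |
| 30 | 25 | 15 | 0 |
| 60 | 55 | 45 | 30 |
| 120 | 115 | 105 | 90 |

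The extremes are 15 - 30 = -15 s and 120 - 5 = +115 s. Most cells are positive, but the sign depends on the assumed inputs. Preparing the covered probe is not counted as a separate item, because the article does not say when it was done or whether it held up the operator.

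**The case against.** The strongest reply is that Procedures says openly what was timed, identically in both groups, and that the outcome list merely uses a shorthand. Treating the listed outcome and the recorded interval as the same thing is an inference. The article condenses a fuller protocol, and neither that nor an analysis plan is shown; either may define the outcome exactly. This stands in part. The inference is nonetheless a strong one, since no other interval is described. A fuller document could rename the outcome, but it could not recover time that was never recorded.

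Three stronger readings are tempting, and the article does not support them.

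- A reader might infer that the outcome leaves out the whole time cost of ultrasound. It does not. Steps (iv) and (v) lie inside the clock, and the two-view wire check has no described counterpart in the control arm.
- A reader might infer a demonstrated bias of a given number of seconds in favour of ultrasound. Control palpation is also untimed, so the bias is a difference between two unmeasured periods. Its direction is plausible rather than shown, and any figure rests on assumed inputs.
- A reader might infer that this undermines the case for wider uptake because time is the main barrier. The article reports survey use of 13% to 27% and availability of 88%, but does not give time as a reason for non-use. It ties practice change to bleeding and vascular complications, and it nowhere claims that ultrasound is faster.

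**Conclusion.** The point holds as a mismatch between an outcome's name and its measurement. The recorded interval runs from anaesthetic to sheath and is not a total access time, whatever the step durations are. It excludes part of the work specific to the ultrasound arm, and only palpation is excluded specifically from the control arm. The comparison is likely, though not provably, tilted towards ultrasound, because a two-part scan should usually take longer than feeling a pulse. The size cannot be derived from the article; the range of -15 to +115 s is illustrative only.

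The conclusion assumes that the listed outcome is the interval described under Procedures and that operators followed the numbered order.

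Severity is minor. This is the last of the other outcomes, below the primary and the key secondary outcomes. The primary result, the sample size of 600 and the power do not depend on it.

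**What to change.** Name the outcome *time from local anaesthesia to sheath insertion* wherever it is listed or reported. State beside it that ultrasound locating and scanning before the anaesthetic, and palpation in the control arm, are excluded. Draw no conclusion on total access time from it.

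This is a change of wording. It needs no new data and could still be made when the article was written, since enrolment was complete but analysis was ongoing. The price is a narrower efficiency claim.

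Fluoroscopy of the femoral head comes first in both arms, so it would be a natural common starting point. Nothing in the article shows that its time was logged. A fluoroscopy-to-sheath time could therefore be reported only as exploratory, and only if logs prove to hold complete times in both arms. It should not replace the recorded outcome after enrolment has closed.

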## Study Outcomes

### Primary outcome

The primary outcome is the composite of BARC 2, 3, or 5 bleeding or major vascular complications (femoral artery pseudoaneurysm, arteriovenous fistula, retroperitoneal bleed, large hematoma of more than 5 cm in diameter, or ischemic limb requiring intervention or surgery) within 30 days (Table 2).^11^

**Table 2 tbl2:** Primary composite outcome definitions

Term	Definition
**Major vascular complication**	
Femoral artery pseudoaneurysm	Diagnosis must be confirmed by US performed by a radiologist demonstrating the following characteristics^27^: 1. Two-dimensional US shows an echo lucent sac that expands and contracts with the cardiac cycle; 2. Color Doppler demonstrates a swirling flow pattern with turbulence inside the echo lucent sac; 3. Pulsed wave Doppler displays a “to-and-fro” signal.
Arteriovenous fistula	Diagnosis must be performed by a radiologist using contrast computed tomography or Doppler US confirming blood flow from the femoral artery into the femoral vein.
Retroperitoneal bleed	Diagnosis must be performed by a radiologist confirming the presence of a hematoma in the retroperitoneal space.
Large hematoma	Diagnosis must be performed by a clinician or nurse, confirming a diameter ≥ 5 cm.
Ischemic limb	Ischemic limb is defined as limb-threatening ischemia, which is confirmed by limb hemodynamics or imaging, and leads to an acute vascular intervention (ie, pharmacologic [heparin or thrombolysis], peripheral artery surgery, peripheral artery angioplasty, or amputation) within 30 days of the procedure.
**Major bleeding**	
BARC 2 bleeding^11^	Any overt, actionable sign of hemorrhage that does not fit the criteria for type 3, 4, or 5 but does meet at least one of the following criteria: 1. Requiring intervention by healthcare personnel; 2. Leading to hospitalization or medical consultation; 3. Requiring medical evaluation.
BARC 3 bleeding^11^	Type 3a 1. Over bleeding plus a hemoglobin drop of 3 to < 50 g/L 2. Overt bleeding requiring transfusion Type 3b 1. Overt bleeding plus a hemoglobin drop of ≥ 50 g/L 2. Cardiac tamponade 3. Bleeding requiring surgical intervention for control 4. Bleeding requiring intravenous vasoactive agents Type 3c 1. Intracranial hemorrhage 2. Intraocular bleed compromising vision
BARC 5 bleeding^11^	Type 5a 1. Probable fatal bleeding Type 5b 1. Definite fatal bleeding with overt bleeding, imaging confirmation, or autopsy

BARC, Bleeding Academic Research Consortium; CT, computed tomography; US, ultrasound.

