## Statistical Considerations

The initial sample size was based on the definition used in the **R**ad**i**al **v**s Femor**al** Access for Coronary Angiography or Intervention (RIVAL) trial in patients with acute coronary syndromes of major vascular complications, and the study used a 3% expected event rate in the control arm and a 1% expected event rate in the experimental arm. These assumptions led to a sample size of 1538 patients, in order to have 80% power with a 2-sided 5% type 1 error level.^12^

A limitation of our initial sample size calculation is that BARC 2 bleeding information was not collected in the RIVAL trial, and therefore it did not have an accurate assessment of event rates. As a result, we re-estimated our sample size based on blinded event rates after enrolling 450 patients. Our revised control event rate was estimated to be 14%. Subsequently, 600 patients were needed to have 80% power, a 2-sided 5% type 1 error level, and a 50% relative risk reduction for the primary outcome. We amended the protocol on April 12, 2021. Power calculations were performed using PASS (version 13, NCSS Statistical Software, Kaysville, UT). Recruitment took longer than expected due to the COVID-19 pandemic halting all non-COVID-19-related research during periods of 2020.

For the primary analysis, an intention-to-treat analysis will include all randomized patients.^13^ In this way, patients will be kept in the treatment group to which they were originally randomized. A secondary as-treated analysis will also be performed. A χ^2^ test or Fisher’s exact test will be performed on a per-patient basis, and statistical significance will be claimed if the *P* value is less than 0.05. Of note, core-lab analyses will be performed on a per-access basis. Odds ratios and 95% confidence intervals will also be reported to quantify treatment effects.

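### The lower hemoglobin bound for BARC type 3a in Table 2 is printed as 3 g/L, probably ten times too low, and needs correcting and checking against what assessors used

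*Protocol article*

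**What the plan says.** The Primary outcome section states: "The primary outcome is the composite of BARC 2, 3, or 5 bleeding or major vascular complications", assessed within 30 days. Table 2 gives the definitions.

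- **Type 3a**, first criterion: "Over bleeding plus a hemoglobin drop of 3 to < 50 g/L". The second criterion is overt bleeding that requires transfusion.
- **Type 3b**, first criterion: "Overt bleeding plus a hemoglobin drop of ≥ 50 g/L".
- **BARC 2**: "Any overt, actionable sign of hemorrhage that does not fit the criteria for type 3, 4, or 5", plus at least one of three care criteria (intervention by healthcare personnel, hospitalization or consultation, medical evaluation).

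Under Other outcomes: "The key secondary outcomes include the individual components of the primary outcome". The article gives no hemoglobin threshold outside Table 2, so nothing in it corrects the type 3a line.

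**The concern.** The type 3a line carries one unit, g/L, and that unit governs both ends of the range. A lower bound of 3 g/L makes almost any re-measured hemoglobin after an overt bleed enough for type 3a, the same type as a bleed that needs transfusion. The line sits in the definition of the primary outcome and states a numeric rule, so it is not a detail left to a fuller document.

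Two things would be at stake if the line were applied as printed. Some bleeds that fail BARC 2 could enter the primary composite. And bleeds that belong in BARC 2 would be counted as BARC 3, which would overstate more severe bleeding in any table that separates the types.

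**Working it through.** **1. Units.** 1 g/dL = 10 g/L.

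| Bound in Table 2 | As printed | In g/dL |
|---|---|---|
| 3a lower | 3 g/L | 3 / 10 = 0.3 |
| 3a upper (exclusive) | 50 g/L | 50 / 10 = 5 |
| 3b lower | 50 g/L | 5 |

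The upper end of 3a meets 3b exactly at 50 g/L (5 g/dL), so the upper bound is on the g/L scale. The figure 3 sits naturally beside 5 only in g/dL, and 3 g/dL × 10 = 30 g/L. The ratio to the printed bound is 30 / 3 = 10. A dropped zero (30 printed as 3) gives the same ratio. The value 30 is an inference from the scale of the neighbouring bound; the article does not print it.

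**2. Internal consistency.** BARC 2 applies only to bleeds that do not meet type 3, 4 or 5. With a 3 g/L bound, any BARC 2 bleed with a measured drop of 3 g/L or more would leave BARC 2. The category would be largely emptied among patients whose hemoglobin was repeated. That makes the printed bound implausible without reference to any outside source.

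**3. What the literal rule would change.** Take overt bleeds with a measured drop of 3 to < 30 g/L, no other type 3 or 5 feature and no major vascular complication. The figure of 30 is the inferred bound.

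| Bleed | Bound of 30 g/L (inferred) | Bound of 3 g/L (printed) | Primary count |
|---|---|---|---|
| Actionable, meets a care criterion | BARC 2, counted | BARC 3a, counted | unchanged |
| Not actionable, or no care criterion met | not counted | BARC 3a, counted | +1 |

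Only the second row alters the primary outcome. It is reduced further because a hematoma that meets the Table 2 size criterion already counts as a major vascular complication, and because a hemoglobin repeated on account of the bleed is arguably medical evaluation, hence BARC 2.

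**4. Sample size.** The article states: "600 patients were needed to have 80% power, a 2-sided 5% type 1 error level, and a 50% relative risk reduction for the primary outcome". With 14% vs 7%, 1:1 allocation and pooled variance under the null, the mean rate is 0.105 and

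n per arm = [1.960 × √(2 × 0.105 × 0.895) + 0.842 × √(0.14 × 0.86 + 0.07 × 0.93)]² / 0.07² = 300 (rounded up),

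which is 600 in total. The stated figure reproduces and does not depend on the hemoglobin bound.

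**5. Pure illustration, not evidence.** Suppose x points of the 14% control rate were minor bleeds unaffected by ultrasound, and the remaining events were halved. The experimental rate is then (14 − x)/2 + x. At 300 per arm, x = 0, 1, 2 and 3 give rates of 7%, 7.5%, 8% and 8.5%, and power of 80%, 73%, 65% and 57%. The article gives no information on x, and x may be close to zero.

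**The case against.** The strongest reply is that this is a transcription slip in a condensed article. The same line misprints the word *Overt*, which is spelled correctly in the next criterion and in type 3b. Each BARC row cites the published definition, and the Discussion says modern BARC definitions are used. The full protocol, case report form and assessor instructions are not shown. This stands: the article does not show that anyone applied 3 g/L.

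Three stronger readings are tempting, and the article does not support them.

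- *Any overt bleed becomes a new primary event, so power is lost.* Actionable bleeds are in the composite already through BARC 2, and movement from BARC 2 to BARC 3 leaves the primary count unchanged. There is no source for the number of added events. The 14% was itself estimated from blinded event rates after 450 patients, so bleeds counted under the definition in use would already be inside it and should not be added on top.
- *BARC 3 is a key secondary outcome.* The article refers only to individual components and does not name BARC 3 among them. The two bold headings in Table 2 also allow a reading with just two components, major bleeding and major vascular complications. On that reading the movement between types changes nothing.
- *The cause is mixed units.* A dropped zero fits equally well.

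The reply does not rescue the printed line. The threshold is part of the primary outcome definition, and a reader of the article has no other value to use.

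**Conclusion.** The point holds as an error in a printed threshold. The type 3a lower bound of 3 g/L is not credible beside a type 3b bound of 50 g/L, and is probably low by a factor of ten. That factor rests on the inference that 30 g/L was meant.

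The consequence is conditional. If the literal bound was used, the primary composite gains only overt, non-actionable bleeds with a measured drop of at least 3 g/L but below the intended bound, and BARC 3 gains events from BARC 2 wherever the types are reported separately. The first effect is narrow and the size of both is unknown. If the bound was correct in the working documents, the error is confined to this table. No loss of power is shown, and the sample size of 600 is unaffected.

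**What to change.** 1. In Table 2, state both type 3a bounds in g/L on one scale, taking the lower bound from the full protocol and the cited BARC definition, and correct *Over* to *Overt*.
2. Before unblinding, confirm which bound the case report form and the blinded assessors used. The Study status section describes data collection and analysis as ongoing, so on this document the check can still be made.
3. Only if the literal bound was used, re-check, without knowledge of allocation, every event classed as 3a on hemoglobin drop alone. Reclassify each as BARC 2 or as not a primary event.

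The cost is one corrected line and one query to the data management team. The blinded re-check in step 3 arises only if the query shows that 3 g/L was applied.
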